### Outcome measures

This is a pragmatic RCT. Therefore, effectiveness will be assessed through a series of questionnaires and clinical exams to study swallowing status and swallowing-related QOL. A complete list of study activities is summarized in Table 1. The follow-up schedule is carefully planned to align with the schedule of cancer surveillance visits that patients attend in usual practice setting. We will evaluate patients to 12 months to examine long-term effectiveness. Capture of outcome intervals have been set with wide, but discrete windows to enhance flexibility. In all arms, off schedule visits are allowable should problems arise, as per usual care. Clinical testing specified in the protocol represents what is standard at institutions that have adopted the PRO-ACTIVE models as routine care.

**Table 1 Tab1:** PRO-ACTIVE Schedule of Activities

	Pre-RT		During RT						Post-RT	
	Baseline		Week 1 ±3 tx days	Week 2 ±3 tx days	Week 3 ±3 tx days	Week 4 ±3 tx days	Week 5 ±3 tx days	Week 6 ±3 tx days	3 Months ±2 weeks	12 Months ±4 weeks
**Time**	**1**	**2** (randomization to 3 tx days after RT Start)	**3**	**4**	**5**	**6**	**7**	**8**	**9**	**10**
**Assessments (by chart abstraction and at clinic visits) and Protocol Procedures**										
Informed Consent	X									
Eligibility verification	X									
VFS^a^	X								X	X
Trismus	X								X	X
Randomization^b^		X								
Demographics	X									
Medical History^c^	X							X	X	X
BMI	X			X		X		X	X	X
PSS-HN^d^	X			X		X		X	X	X
RT plan archive^e^								X^i^		
AESI				X		X		X	X	X
Pain Medications	X							X	X	X
Trigger Review**			(X)	(X)	(X)	(X)	(X)	(X)		
**Swallowing Therapy**										
Swallowing Therapy Sessions^f^		X		X		X		X		
**Patient Reported Outcomes (does not require clinic visits)**										
Trigger PRO***			(X)	(X)	(X)	(X)	(X)	(X)		
MDADI	X							X^i^	X	X
Tube PRO	X			XX		XX		XX	X^j^	X^k^
MDASI-HN	X			X		X		X	X	X
Exercise Diary			X*	X*	X*	X*	X*	X*	X	X
MOD^g^	X								X	X
Self-Report Pneumonia^h^	X								X	X
CBI-I	X								X	X
EQ-5D-5L	X								X	X

(X) Only for untriggered RE-ACTIVE arm participants

XX Only for Triggered RE-ACTIVE Arm 1, PRO-ACTIVE EAT and PRO-ACTIVE EAT + EXERCISE Arm 3 participants

X* Only for Triggered RE-ACTIVE Arm 1 and PRO-ACTIVE EAT + EXERCISE Arm 3 participants

^a^ X-Ray involved. Requires central lab review

^b^ randomization completed within 72 h of eligibility verification by completion of central VFS review

^c^ Per chart abstraction by coordinator; if missing in chart, by coordinator contact

^d^ Validated clinic interview along with study specific questions administered by SLP/Clinician (or by a research coordinator if no clinic visits or missed in clinic)

^e^ RT plan DICOM archived to central database

^f^ Conducted by Speech Language Pathologist and only for participants assigned to PRO-ACTIVE arms. Participants in RE-ACTIVE arms who are triggered will begin swallowing therapy according to the EAT-EXERCISE model in arm 3 (PRO-ACTIVE EAT + EXERCISE) within 3 treatment days

^g^ to be completed at select sites only

^h^ administered as part of MOD

^i^ completed at the end of RT

^j^ to be completed every 2 weeks for first 3 months after RT within ±3 days

^k^ to be completed monthly within ±7 days

**Coordinator review of trigger status of RE-ACTIVE participants

***Participant review of PRO dependent trigger items (i.e. tube feed and MDASI #16 choke item)

#### Primary outcome

The primary endpoint of duration of feeding tube dependence was selected because of its high relevance and clear importance to both patients and providers [35, 36]. Maintaining the ability to swallow foods and liquids is the primary functional priority ranked by HNC patients both before and after their treatment [35, 37]. Because feeding tube utilization requires greater resource burden, this endpoint is also relevant to administrators and payers who make decisions about whether to support a healthcare service by way of reimbursement, staffing, or endorsement as best practice. Feeding tube dependence is also pragmatic as a primary endpoint because it is universally measured in usual care, that is, providers ask about and document feeding tube status at routine clinical visits. Therefore, our primary endpoint of feeding tube use can be ascertained by medical chart, in clinic, or by our study specific electronic PRO (ePRO) remotely. A participant will be considered lost to follow-up if feeding tube use cannot be ascertained by any means at 12 months post RT.

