The Cancer Behavior Inventory was developed as a comprehensive measure of self-efficacy strategies for coping with cancer, drawing from self-regulation and self-efficacy theories [57–59]. The most recent version of 27 items has undergone extensive revision to ease administration and strengthen psychometric properties. The measure is designed at a grade 6 reading level and has 7 subscales or factors including Maintaining Activity and Independence, Seeking and Understanding Medical Information, Emotion Regulation, Coping with Treatment Side Effects, Accepting Cancer/Maintaining a Positive Attitude, Seeking Social Support, and Using Spiritual Coping. Internal consistency is reported as Cronbach’s alpha of .946, and test-retest reliability as *r* = .890 (4 months) with mixed groups of cancer patients [60]. Validity coefficients indicate strong psychometric properties with higher scores on the CBI associated with better adjustment to cancer, higher quality of life, and lower levels of emotional distress. Each item presents an activity a cancer patient might do during and after cancer treatment and is scored on a Likert type scale ranging from 1 (*‘not at all confident’*) to 7 (‘*totally confident’*). Scores are derived for each of the subscales as well as an overall total score.
7)EQ-5D-5L

EQ-5D-5L is a modified version of the widely used EuroQOL 5 Dimension [61]. The brief 6-item EQ-5D-5L questionnaire is used to describe and value health. The EQ-5D-5L descriptive system measures five levels of severity in each of the existing five dimensions (mobility, self-care, usual activities, pain/discomfort, and anxiety/depression). The questionnaire also contains a Visual Analog Scale, by which respondents can report their perceived health status with a grade ranging from 0 (the worst possible health status) to 100 (the best possible health status).
8)Medical History

Intake details, radiation therapy details, systemic therapy/chemotherapy details, tumour status, surgery history, tracheotomy, feeding tube insertion, removal, and use dates, feeding tube dependence, concomitant swallowing therapies, vital status, BMI, and complication details will be collected by review of patient medical record at specified intervals.
9)Pain Medications

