### Statistical analysis

#### Primary endpoint

For the primary endpoint, an intention-to-treat (ITT) approach will be applied incorporating a gate-keeper method to control risk of Type 1 error in the setting of multiple comparisons [64, 65]. The primary hypothesis (Hyp 1.1) is that the combined PRO-ACTIVE interventions (PRO-ACTIVE EAT and PRO-ACTIVE EAT+EXERCISE) will result in a better swallow outcome compared to RE-ACTIVE as measured by duration of feeding tube use in the first year after the completion of RT. If PRO-ACTIVE is superior in Hyp 1.1, we will assess the dose response of the PRO-ACTIVE arms. The secondary hypothesis (Hyp 1.2) is that the most intensive intervention (PRO-ACTIVE EAT+EXERCISE) will be more effective than the least intensive (PRO-ACTIVE EAT).

The initial analysis will compare the RE-ACTIVE group to the combined PRO-ACTIVE groups in terms of the duration of feeding tube use operationalized as count of days of tube use from end of RT to last tube use within the 12-month study period by means of a multiple linear regression model with covariate adjustment. The presence of a feeding tube which is not being used for feeds is disregarded. The treatment effect will be expressed as absolute mean difference along with 95% confidence intervals. If this test yields *p* < 0.05, the two PRO-ACTIVE groups (EAT versus EAT+EXERCISE) will be compared using the same linear analysis method. The meaningful variables we will include in the regression model are: age (as a continuous variable); HPV status (oropharyngeal site vs all others); surgery (yes/no); chemotherapy (yes/no); radiation dose (as a continuous variable); and, facility (as a categorical variable to account for practice variation across the eleven sites).

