The largest threat of missing data is non-random loss of outcomes data for the primary endpoint. Missing data for the primary endpoint is extremely unlikely because it is a simple variable that can be ascertained in clinic or remotely via telephone/web interview of the patient. Non-random missing data is more likely for outcomes requiring clinic examination (i.e., videofluoroscopy) for which we have estimated attrition at 26% based on prior longitudinal work from the investigators [38]. For outcomes missing in > 10% of patients, we will consider multiple approaches. One method we may employ is inverse probability weighting approach to account for statistical uncertainty due to missingness. Another option we will explore is multivariate imputation using chained equations [66]. When similar inferences are derived from complete case analysis and imputation, we will report complete case analysis results for simplicity and transparency.

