### Sample size calculation

Sample size calculations, based on a 2-sample t-test, assume 952 patients enrolled with 1:4 allocation to RE-ACTIVE (Arm 1, *n* = 190) and PRO-ACTIVE arms (Arms 2 and 3, *n* = 381 per group). The attrition factor is set at 5% because the primary endpoint can be ascertained without clinical encounter. Thus, the resultant sample size estimated is 180 in Arm 1, 361 in Arm 2, and 361 in Arm 3. For the primary comparison (Hyp 1.1) of Arm 1 (*n* = 180) versus the combined Arms 2 and 3 (*n* = 722), assuming ITT analysis with type 1 error probability of 0.05 (two-sided) yields 80% power to detect a small effect size of .23 SD for duration of feeding tube use. For the analysis of Hyp 1.2 in the gate-keeper approach, we will compare intensity of PRO-ACTIVE therapies (Arm 2 versus Arm 3, *n* = 361 per group), assuming type 1 error probability of 0.05 (two-sided), we have 80% power to detect again a small effect size of 0.21 SD for the primary endpoint of feeding tube duration. We expect the t-test will not be sufficient as the primary analysis given it does not allow for covariate adjustment. Therefore, we will apply the multiple linear regression model as the primary analysis for Aim 1. The power calculation conducted assuming t-tests for analysis of hypotheses 1.1 and 1.2 and deriving a sample of 952 patients remain sufficient for the linear model because by adjusting for variables associated with the mean response, the distribution of the residuals is expected to improve. Therefore, the power for the same hypothesized difference in the primary outcome attributed to treatment in the regression framework will be at least as much as for that for the t-test.

For the secondary analysis (Aim 2) in the gate-keeper approach, we will compare intensity of PRO-ACTIVE therapies (Arm 2 versus Arm 3, *n* = 361 per group), assuming type 1 error probability of 0.05 (two-sided), we have 80% power to detect again a small effect size of 0.24 SD for PROs and VFS measures. The attrition factor for the secondary analysis is set at 26% because they are more prone to attrition due to required clinical visits and survey responses required from participants. As an exception, feeding tube dependence at 3-months uses an attrition factor of 5%, for the same rationale as the primary endpoint.

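### Loss to follow-up is judged by tube use at 12 months, but the endpoint is a dated duration, and the stated missing-data rules point to a complete-case analysis at the planned 5% loss

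*Protocol article*

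**What the plan says.** **Follow-up rule** (Outcome measures, Primary outcome): "A participant will be considered lost to follow-up if feeding tube use cannot be ascertained by any means at 12 months post RT". The preceding sentence names the sources: "our primary endpoint of feeding tube use can be ascertained by medical chart, in clinic, or by our study specific electronic PRO (ePRO) remotely".

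**Endpoint** (Statistical analysis, Primary endpoint): duration is operationalised as a "count of days of tube use from end of RT to last tube use within the 12-month study period", compared by linear regression under ITT.

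**Dated tube data collected:**
- Tube PRO every 2 weeks for the first 3 months after RT, then "to be completed monthly within ±7 days" (Table 1 footnotes).
- From the chart, "feeding tube insertion, removal, and use dates" (Secondary outcomes, Medical History). Under a Table 1 footnote, the coordinator contacts the participant if the chart is silent.
- Tube questions added to the PSS-HN, which is scheduled at 3 and 12 months.

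**Missing data** (Statistical analysis, Primary endpoint): non-random loss of the primary endpoint is named as the largest threat, but then "Missing data for the primary endpoint is extremely unlikely because it is a simple variable". On methods: "For outcomes missing in > 10% of patients, we will consider multiple approaches". Complete-case results are reported when they agree with imputation.

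**Sample size** (Sample size calculation): attrition of 5%, justified by ascertainment without a clinic encounter. "Thus, the resultant sample size estimated is 180 in Arm 1, 361 in Arm 2, and 361 in Arm 3".

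**The concern.** The follow-up rule asks about one time point, while the endpoint asks when tube use stopped. The two can disagree in both directions.

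A participant whose last tube use was documented at month 2, and who kept reporting until month 10, is lost under the rule if nothing can be learned at month 12. Yet 10 of the 12 months are observed, and the duration is about 60 days unless use resumed. Conversely, a participant known to be tube-free at month 12 is not lost, even if the date of last use was never captured.

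The claim that missing data are extremely unlikely, and the 5% attrition, both rest on how easily current tube status can be found out. That does not show that the stop date will be known.

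At stake is possible bias in the primary comparison. Participants and therapists are not blinded, and the Study withdrawals section allows withdrawal for adverse events, medical conditions or a change to palliative intent. Loss could therefore be related to health and could differ by arm.

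**Working it through.** **1. The plan's own figures.** Inputs from Sample size calculation: 190, 381 and 381 randomised; 5% attrition; two-sided 0.05; 80% power; targets of 0.23 SD (Hyp 1.1) and 0.21 SD (Hyp 1.2).

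- Attrition: 190 × 0.95 = 180.5 and 381 × 0.95 = 361.95, against the stated 180 and 361.
- Hyp 1.1, 180 v 722: standard error = √(1/180 + 1/722) = 0.0833 SD. Detectable difference = (1.960 + 0.842) × 0.0833 = 0.233 SD. Power at 0.23 SD = Φ(0.23/0.0833 − 1.960) = 78.8%.
- Hyp 1.2, 361 v 361: standard error = √(2/361) = 0.0744 SD. Detectable difference = 0.209 SD. Power at 0.21 SD = 80.5%.

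Both stated figures reproduce, allowing for rounding of the effect sizes.

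**2. What the lost participants cost in power (Hyp 1.1 at 0.23 SD).**

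| Share lost | Power |
|---|---|
| 0% | 81.0% |
| 5% (planned) | 78.9% |
| 10% (assumed) | 76.8% |

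The 5% row uses unrounded numbers (180.5 and 723.9). Keeping every lost participant would gain at most 81.0 − 78.9 = 2.1 points, so power is not the issue.

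**3. How the rules combine at the planned loss.** The analysed numbers exclude 952 − (180 + 361 + 361) = 50 people, which is the 5% after rounding. Since 5% is below the threshold of more than 10%, the article names no weighting or imputation step for the primary endpoint. What is left is regression on those whose endpoint is counted as available.

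**4. Possible bias.** Suppose a share d of one arm is left out and those people differ by D SD, on average, from those kept, with no such difference in the other arm. The complete-case estimate then shifts by d × D. The article gives neither D nor loss by arm, so D and the one-sided pattern are assumptions.

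| d | D (SD) | Shift (SD) | Share of 0.23 SD |
|---|---|---|---|
| 5% | 0.25 | 0.0125 | 5% |
| 5% | 0.5 | 0.025 | 11% |
| 5% | 1 | 0.05 | 22% |
| 10% | 0.25 | 0.025 | 11% |
| 10% | 1 | 0.10 | 43% |

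Equal loss with equal D in both arms would cancel. The shift is the whole complete-case bias; retained histories can remove only the part due to people who have a usable history.

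**5. How uncertain a stop date can be.** If the Tube PRO is completed as scheduled, last use is bracketed to about 2 weeks up to month 3 and about 1 month after that. In the worst case, a participant last seen using the tube at month 3, tube-free at month 12 and with no source in between has a duration anywhere from about 91 to 365 days.

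**The case against.** A reader might infer that the protocol drops participants with nearly complete histories and counts 12-month responders without a stop date as complete. The article does not say either. Its follow-up sentence is a disposition label, the analysis is called ITT, and the Study withdrawals section does not say that data already collected are discarded. Taking 5% off the planned numbers is ordinary planning for power and does not define who is analysed. Feeding tube use in that sentence may also be shorthand for the endpoint as a whole, since the preceding sentence uses it that way. All of this stands, so exclusion is an inference from how the rules combine.

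The 12-month responder with no stop date is also a narrow case. Chart use dates, coordinator contact and the PSS-HN tube questions would all have to fail along with the Tube PRO. Such participants should be a minority.

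Finally, detailed handling of partial histories commonly belongs in the SAP, which is not shown, so its absence here is no finding. The objection does not remove what the article itself fixes: a follow-up rule tied to one time point, a missingness claim that fits status better than duration, and a threshold that leaves the primary endpoint without a named method at the planned loss.

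**Conclusion.** The concern holds in a limited form. The follow-up rule does not fit the endpoint. Read together with the attrition allowance and the threshold of more than 10%, it leads naturally to a complete-case primary analysis at 5% loss, with collected tube histories unused. That is the likely consequence of the stated rules, not something the article declares.

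No sample-size figure is wrong. The possible bias is modest: 0.0125 to 0.05 SD, or about 5% to 22% of the 0.23 SD target. This assumes that 5% of one arm is lost, differs by 0.25 to 1 SD from those kept, and has no counterpart in the other arm. The change is worth making because part of that bias can be avoided with data the trial already plans to collect.

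**What to change.** 1. Define missingness of the primary endpoint by whether the last-use date, or continuing use to 12 months, is known. Base the expected missingness on that definition.
2. Keep all Tube PRO, PSS-HN and chart tube data to last contact in the ITT analysis, whatever the 12-month status.
3. Impute the unobserved remainder, and stop dates known only to an interval, within their known limits. For someone lost, these run from no further use to use until month 12. Add a sensitivity analysis at those bounds.
4. Apply this to the primary endpoint at any level of missingness, not only above 10%.

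The cost is wording in the protocol or SAP and some extra analysis; no new data are needed. Stated missingness may look slightly less favourable once unknown stop dates are counted. If the SAP already contains these rules, aligning the follow-up definition and the missing-data paragraph with it is enough.

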#### Secondary outcomes

Secondary outcome measures represent both clinician-graded and patient reported outcome (PROs) measures. These measures were selected based on feasibility [38] at all sites, psychometric validation, familiarity to the investigative team, and/or wide used in routine settings of care, thereby maintaining pragmatic standards. The secondary outcomes are the following:
The MD Anderson Dysphagia Inventory (MDADI)

MDADI is a widely used PRO instrument to evaluate swallowing-related QOL in HNC patients [39]. The 20-item questionnaire quantifies an individual’s global, physical, emotional, and functional perceptions of swallowing ability. MDADI was internally developed and validated at MD Anderson Cancer Center and has been integrated in the MDACC dysphagia clinic for more than 10 years. Questionnaire development included engagement of providers and patients with HNC who experienced dysphagia iteratively throughout conception and refinement of the final scale. In a validation sample of 100 patients with HNC, concurrent validity was moderate by comparison with the Performance Status Scale-Head and Neck (Spearman correlation, 0.47-0.61). Correlation with the subscales of SF-36 demonstrated convergent and divergent validity of the MDADI. Test-retest reliability (physical, 0.86; emotional, 0.88; functional, 0.88) and internal consistency reliability (overall Cronbach’s alpha, 0.96) were sound [39]. Subsequent validation studies further demonstrated suitable psychometric properties in patients with different ethnic-cultural backgrounds [40–42]. Perceived dysphagia as quantified by the MDADI is time-dependent, radiotherapy dose-dependent and varies by extent of surgery and tumor site in HNC samples [35, 43]. The investigators have previously shown a 10-point between-group difference to discriminate a clinically meaningful difference in swallowing outcome [44].
2)The MD Anderson Symptom Inventory for Head and Neck Cancer (MDASI-HN)

MDASI-HN is a multi-symptom PRO instrument designed to measure severity or burden of cancer-related symptoms and their interference with or effect on patients’ daily functioning [33, 45]. Symptom burden refers to the severity of physical or mental experience by a patient with a specific symptom. Symptom measures are more specific and direct than QOL measures and thus are more sensitive to treatment-related changes. The 28-item MDASI-HN multi-symptom inventory measures include 13 core items (“systemic symptoms”: pain, fatigue, sleep, etc.), 9 head and neck specific items (“local symptoms”: dry mouth, mucus, shortness of breath, taste, etc.), and 6 interference items (activity, work, relations, etc.). The core MDASI items were validated for use in cancer patient populations regardless of the specific diagnosis or type of therapy [45] and thus can be used to compare symptom burden between different types of cancer. The 9 head and neck specific items were validated internally at MDACC with regard to construct and concurrent validity in a cohort of 205 HNC patients [33]. Internal consistency reliability is high in the core MDASI score, the 9 head and neck-specific items, and the 6 interference items (Cronbach’s α: 0.72–0.92). MDASI-HN can be completed in less than 7 min. MDASI-HN offers quantification of overall symptom burden, but also 2 dysphagia-specific items (“difficulty swallowing”, “choking”) and will be used to understand and adjust for symptoms such as mouth sores, pain, or dry mouth, that make eating challenging during RT. The investigators have experience in using MDASI-HN in weekly radiation clinics for symptom monitoring with a resultant publication characterizing the evolution and cumulative increase in symptoms weekly during HNC RT [46]. Symptom burden can be considered both a secondary outcome, but also a potential confounder (i.e., competing toxicity) that may influence adherence to swallowing therapy.
3)Videofluoroscopic Swallow (VFS) Studies

The VFS is a dynamic, radiographic imaging study, in which the patient is administered radiopaque labeled bolus volumes in a series of standardized liquid and solid food consistencies to examine oropharyngeal swallow physiology, aspiration, and/or pharyngeal residue. VFS is considered a gold standard measure of dysphagia in clinical practice and is routinely conducted by speech language pathologists in medical settings*.* Digital videos from VFS will be scored centrally by a trained speech language pathologist blinded to clinical history using the following measures: DIGEST [32], pharyngeal constriction ratio (PCR) [47], penetration-aspiration scale (PAS) [48] and maximum pharyngoesophageal segment opening (PESmax) [49]. DIGEST, the primary measure to determine study eligibility, was developed and validated by the study team [32] as a CTCAE compatible VFS-derived severity grade of pharyngeal dysphagia. DIGEST is reliable (intra- and inter-rater weighted *k* 0.82–0.84 and 0.67–0.81, respectively) and discriminates pharyngeal pathophysiology (MBSImP™©:*r* = 0.77, *p* < 0.001), perceived dysphagia (MDADI: *r* = − 0.41, p < 0.001), and diet (PSS-HN: *r* = − 0.49, p < 0.001) in HNC survivors [32]. DIGEST is sensitive to change in swallowing function over time [50]. PCR, the primary endpoint of VFS for secondary analysis (**Aim** 2), is a continuous measure of pharyngeal swallowing strength. PCR is a pixel based measure computing area of the pharynx at maximum constriction at peak swallow over the resting area of the pharynx from the mid-sagittal radiograph. PCR provides a reliable radiographic surrogate measure of pharyngeal strength (measured against gold standard pharyngeal manometry) [47, 51, 52] and discriminates aspiration status in dysphagia populations [52]. PAS is an 8-point ordinal classification of swallow airway safety capturing bolus penetration and aspiration, where a score of 1 indicates no airway entry, 2–5 indicates penetration, and 6–8 indicates aspiration. PAS ratings are highly reliable (ICC for inter- and intra-rater reliability: 0.96 and 0.95–0.97, respectively) and predictive of aspiration pneumonia after chemoradiation (*p* < 0.001, AUC = 0.72) [1]. PESmax provides a reliable radiographic surrogate marker of stricture at the level of the cricopharyngeal muscle, which if present will critically disrupt transport of the bolus into the esophagus [53].
4)Performance Status Scale Head and Neck (PSS-HN)

The PSS-HN [54] is a 3-item validated semi-structured interview tool capturing normalcy of diet, public eating, and, understandability of speech. Each item is scored from 0 to 100, with the higher score indicating better performance. The PSS-HN correlated well with the FACT-HN, especially for normalcy of diet and eating in public (r = 0.66, *p* < 0.0001; r = 0.42, p < 0.0001, respectively) and is a reliable tool, sensitive to differences in functioning when applied to HNC patients [55]. The PRO-ACTIVE trial adaptation of PSS-HN includes additional questions regarding tracheotomy status and feeding tube utilization.
5)Medical Outcome of Dysphagia (MOD)

The Medical Outcomes of Dysphagia (MOD) is a newly developed 3-part inventory that targets patient reported symptoms related to health consequences secondary to dysphagia, namely: malnutrition (MOD-Nutrition), aspiration pneumonia (MOD-Pulmonary) and mood changes such as depression and anxiety (MOD-Psychology) [56]. The MOD-Nutrition sub-scale consists of 13 items, of which all but one have either a 3, 4 or 5-point ordinal response; the remaining item quantifies food intake. The MOD-Pulmonary sub-scale consists of 11 items, of which all have a 5-point ordinal response. Likewise, the MOD-Psychology sub-scale consists of 45 items, of which all have a 5-point ordinal response. The study assessing reliability and divergent validity of the items in the three MOD subscales has recently been completed, and included over 350 patients, among whom 77% had a diagnosis of dysphagia secondary to head and neck cancer. Each of the sub-scales has excellent inter-rater reliability with the following total score ICC (95% confidence interval): MOD-Nutrition, ICC = 0.84 (0.73–0.91); MOD-Pulmonary, ICC = 0.89 (0.81–0.94); and, MOD-Psychology ICC = 0.90 (0.83–0.94). The items on the MOD were derived from an extensive review of the literature combined with collective opinion of clinicians, patients and caregivers [56].
6)Cancer Behavior Inventory – Version 3 (CBI-V3)

The Cancer Behavior Inventory was developed as a comprehensive measure of self-efficacy strategies for coping with cancer, drawing from self-regulation and self-efficacy theories [57–59]. The most recent version of 27 items has undergone extensive revision to ease administration and strengthen psychometric properties. The measure is designed at a grade 6 reading level and has 7 subscales or factors including Maintaining Activity and Independence, Seeking and Understanding Medical Information, Emotion Regulation, Coping with Treatment Side Effects, Accepting Cancer/Maintaining a Positive Attitude, Seeking Social Support, and Using Spiritual Coping. Internal consistency is reported as Cronbach’s alpha of .946, and test-retest reliability as *r* = .890 (4 months) with mixed groups of cancer patients [60]. Validity coefficients indicate strong psychometric properties with higher scores on the CBI associated with better adjustment to cancer, higher quality of life, and lower levels of emotional distress. Each item presents an activity a cancer patient might do during and after cancer treatment and is scored on a Likert type scale ranging from 1 (*‘not at all confident’*) to 7 (‘*totally confident’*). Scores are derived for each of the subscales as well as an overall total score.
7)EQ-5D-5L

EQ-5D-5L is a modified version of the widely used EuroQOL 5 Dimension [61]. The brief 6-item EQ-5D-5L questionnaire is used to describe and value health. The EQ-5D-5L descriptive system measures five levels of severity in each of the existing five dimensions (mobility, self-care, usual activities, pain/discomfort, and anxiety/depression). The questionnaire also contains a Visual Analog Scale, by which respondents can report their perceived health status with a grade ranging from 0 (the worst possible health status) to 100 (the best possible health status).
8)Medical History

Intake details, radiation therapy details, systemic therapy/chemotherapy details, tumour status, surgery history, tracheotomy, feeding tube insertion, removal, and use dates, feeding tube dependence, concomitant swallowing therapies, vital status, BMI, and complication details will be collected by review of patient medical record at specified intervals.
9)Pain Medications

All pain medications, including over-the-counter medications, reportedly taken in the past 48 h are noted on the pain medication form in the case record form (CRF) at pre-specified intervals (e.g. baseline, week 6 of RT, 3 months and 12 months post RT).
10)Mouth Opening/Trismus

Interincisal opening will be measured at baseline, and 3 months and 12 months post RT using a standardized TheraBite® Range of Motion Scale (TRMS) [62]. Reference points will be noted (gingiva and/or teeth) on the study case report form.
11)Hospitalization/ Emergency Department Presentation

Hospitalization and/or emergency department presentation will be abstracted from the medical record and by asking participants to identify such events to any external institutions anytime during their participation in the trial.

